**10.6.4.e Analyses**

*Measurement of Serum Creatinine, Calcium, Cystatin C, Phosphate. Alkaline phosphatase, FGF-23 and intact PTH*

At the Albert Einstein College of Medicine Institute for Clinical and Translational Research laboratory, specimens will be received and appropriately stored until analysis. Analyses will be batched and analyses will be performed once all of the specimens are received.

*Measurement of urinary albumin, creatinine, KIM-1 and NGAL*

Analyses will be batched and performed by the Albert Einstein College of Medicine Institute for Clinical and Translational Research laboratory using standard methods.

*10.6.5 Sample Size and Power*

Of the 2259 participants in the parent study, we plan to recruit approximately 900 into this sub-study. In the Framingham Offspring cohort with a mean age of 59 years, 12.2% had microalbuminuria, defined as at least 30 mg/g creatinine. [186](#_ENREF_186) In the NHANES III survey, which includes younger participants, 8.5% of participants had a urinary albumin:creatinine ratio greater than 30 mg/g.[187](#_ENREF_187) Assuming the background prevalence of microalbuminuria in the trial is 12% and an alpha of 0.05, we will have 80% power to detect a relative risk of 0.64 for microalbuminuria comparing the vitamin D groups to the placebo group with 900 participants. We will therefore aim to recruit 900 participants for the urinary albumin measurement. In the Framingham Offspring Study, the standard deviation for systolic blood pressure is approximately 20 mm Hg. [186](#_ENREF_186) Assuming an alpha of 0.05 and 900 participants, we will have greater than 85% power to detect a difference of 3 mm Hg between the vitamin D and placebo groups. For the repeated measures analysis for creatinine we will only use data from participants who have had all of their creatinines measured at the same laboratory (n≈1500). Having a sample size of 1500 for repeated measures analysis to evaluate changes in creatinine with an alpha of 0.05 gives us 90% power to detect a difference of 0.1 mg/dL in creatinine measurements. Evaluating changes in bone serum biomarkers, assuming an alpha of 0.05, we have >90% power to detect a difference of 1 standard deviation between the groups.

*10.6.6 Statistical Analyses*

Specific Aim #1: All analyses will be performed and outliers will be verified by re-assay, if urine is available. Because this is a post-hoc analysis of a randomized clinical trial and data will not be available on the entire clinical trial population, we will create a table to evaluate whether baseline characteristics are equally distributed among the participants in the sub-study. The proportion of participants in each randomized group with microalbuminuria (defined as >30 mg/g creatinine) will be compared using a chi-square test. If there are imbalances in the baseline characteristics, we will perform a logistic regression with the outcome albuminuria adjusting for characteristics that were imbalanced at baseline. In addition, we will compare medication use at follow-up to evaluate whether there were imbalances in NSAID and ACE inhibitor and Angiotensin Receptor Blocker (ARBs) use between the randomized groups.

Specific aim #2: The mean blood pressure of the 3 measurements will be used for all analyses. Baseline characteristics of the randomized groups included in this sub-study will be compared. In addition, the use of anti-hypertensive medications at the time of the blood pressure measurement will be compared between the groups. We will first compare the systolic and diastolic blood pressures among the 4 randomized groups using ANOVA. We will also compare vitamin D to no vitamin D using Student’s t-test. If characteristics are not balanced between the groups, we will use multivariable adjusted linear regression to evaluate whether treatment had an effect on systolic and diastolic blood pressures separately.

Specific aim #3: All data will be checked for outliers and specimens will be re-assayed for extreme outliers. Creatinine measurements will be converted to estimated glomerular filtration rates using the CKD-Epi equation. [188](#_ENREF_188) We will compare the prevalence of CKD (defined as an estimated GFR <60 ml/min/1.73m2) between the 4 treatment arms using chi-square test. We will also used random effects models with repeated creatinine measures which can account for missing values to compare serial creatinines between the 4 treatment groups. To evaluate whether calcium and/or vitamin D supplementation over 5 years affected serum phosphate, alkaline phosphatase, intact PTH and FGF-23 levels, we will compare levels between the intervention groups and the placebo group using appropriate methods for skewed data.

*10.6.7 Human Subjects Research*

*10.6.7.a Human Subjects Involvement and Characteristics*

The participants in this ancillary study are already enrolled in a 3 to 5-year randomized clinical trial of calcium and/or vitamin D. They have already consented to participate in the parent study. For this ancillary study, they will undergo an additional informed consent procedure during their end-of-treatment visit for the parent study and, if consented, will have their blood pressure measured, give a urine sample and have additional blood samples taken at the end-of-treatment blood draw for the parent study.

We expect that the population for this sub-study will be similar to that of the overall parent study. The mean age at enrollment was 58.1 (standard deviation 6.8), the participants were 37% female and 83% white, 8.1% black, 8.5% other race and 6.5% of Hispanic ethnicity.

The study will take place at the sites of the parent trial: Dartmouth Hitchcock Medical Center, Cleveland Clinic Foundation, University of Colorado, Emory University, University of Iowa, University of Minnesota, University of North Carolina, University of South Carolina, University of Southern California, University of Texas and University of Puerto Rico and their related practice sites.

*10.6.7.b Sources of Materials*

The participants in this sub-study will give urine and blood samples and will have their blood pressures measured. The parent study is collecting information on demographics, co-morbid health conditions, medications and other health information. The new data will be linked to existing data via unique identifiers.

*10.6.7.c. Potential Risks*

The additional physical risks associated with the sub-study are those associated with the collection of the urine, blood and blood pressure, which are outside of the standard of care. Drawing blood, or venipuncture, may result in bruising to the arm or on rare occasions, vasovagal syncope. Blood pressure measurements involve some discomfort as the sphygmomanometer is inflated. There are no significant risks to a spot urine collection. All these risks are detailed in the informed consent document. There may be additional risks of breach of confidentiality with the additional measurements taken. All study personnel are already trained in the importance of maintaining confidentiality and all data for analysis at the Albert Einstein College of Medicine will be de-identified.

*10.6.7.d. Adequacy of the Protection against Risks*

*10.6.7.d.1 Recruitment and Informed Consent*

All patients included in this sub-study have already undergone 3 or 5 years of a randomized clinical trial with blood testing and colonoscopies. They will undergo a separate informed consent process for this sub-study detailing the rationale for the study and risks and benefits associated with participation.

*10.6.7.d.2. Protection against Risk*

All staff are trained to maintain complete confidentiality. All data transferred to the Albert Einstein College of Medicine will be completed de-identified. Venipuncture and blood pressure measurements will be conducted by experienced phlebotomist and technician with the patient seated. The Data and Safety Monitoring Committee for the parent trial will serve in this capacity for the ancillary study, by monitoring for potential complications and recommending whether the trial should continue.

10.6.7.e. Potential Benefits of the Proposed Research to the Subject and Others

The participants of this trial will likely not directly benefit from the kidney functions ancillary study. However, the results of this trial may impact the treatment for patients with kidney disease and high blood pressure with an inexpensive therapy, calcium and vitamin D.

*10.6.7.f. Importance of Knowledge to be Gained (Risk: Benefit Ratio)*

High blood pressure, kidney disease and microalbuminuria are all associated with high risk of cardiovascular disease and mortality. A new, inexpensive therapy to treat high blood pressure, prevent the progression of kidney disease and/or albuminuria would have far-reaching public health implications. The risks to the participant for this ancillary study are fairly minimal and involve the collection of blood, urine and blood pressure measurements at a single time point at the end of a randomized clinical trial evaluating colonic polyp recurrence. The risks detailed above are fairly minimal in comparison to the knowledge to be gained.

*10.6.7.g. Data Safety Monitoring Plan*

The Data and Safety Monitoring Committee for the parent trial will serve in this capacity for the ancillary study, by monitoring for potential complications and recommending whether the trial should continue.

*10.6.7.h. Inclusion of Women and Minorities*

We expect that the participants in the kidney function sub-study will have the same gender and race/ethnicity make-up as the parent trial. Therefore we expect 37% female participants and 83% white, 8.1% black, 8.5% other race and 6.5% of Hispanic ethnicity. We will not exclude any participants based on gender or race/ethnicity.

10.6.7.i. Inclusion of Children

Children are not enrolled in the parent study, the Vitamin D Polyp Prevention Trial because children generally do not get colonic polyps and if they do occur in children, they are part of a genetic syndrome and probably would not be affected by vitamin D and calcium supplementation. Therefore, no children will be recruited into the kidney functions sub-study.

*10.7* Participant Beliefs and Bias Study

This ancillary analysis is under the direction of [name] at the Geisel School of Medicine at Dartmouth.

*10.7.1 Background and rationale*

The randomized, placebo-controlled trial uses allocation concealment and blinding of participants and investigators to minimize bias in patient selection, adherence, and ascertainment of outcomes. Beliefs about the assigned treatment (allocation belief) and its efficacy (efficacy belief), and treatment preference may affect adherence, health behaviors, attrition, and health endpoints. We will study the relations between these beliefs, blinding, adherence and health outcomes. Our findings will help develop strategies to prevent and/or correct for belief-related biases in future trials.

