Thus far, vitamin D and phosphate binding therapies have not yet been tested in a large randomized clinical trial powered to evaluate kidney disease outcomes. The Vitamin D/ Calcium Polyp Prevention Study is the ideal setting in which to test the effects of vitamin D and/or calcium on kidney function in a double blind, placebo controlled setting.

*10.6.2 Objectives*

The primary aim is to investigate the effect of calcium and/or vitamin D on the prevalence of microalbuminuria, a marker of kidney damage, at the end of 3 or 5 years of treatment with calcium and vitamin D, calcium alone or vitamin D alone versus placebo.

*Hypothesis: Vitamin D treatment will be associated with a lower prevalence of microalbuminuria.*

The secondary aims are as follows:

1. To evaluate the effects of calcium and/or vitamin D on blood pressure at the end of 3 or 5 years of treatment with calcium and vitamin D, calcium carbonate alone or vitamin D alone versus placebo.

*Hypothesis: Vitamin D therapy will be associated with significantly lower blood pressure.*

1. To evaluate the effects of calcium and/or vitamin D on kidney function as measured by serum creatinine measurements at baseline, year 1, year 3 and year 5 in all participants of the parent study with available creatinine measurements. Additional urine and serum markers of kidney function to be measured at the end of 3 to 5 years of treatment will include:
   1. Urine: markers of tubular damage including KIM-1 and NGAL
   2. Serum: creatinine (to be assayed at the lab used for baseline measurement),calcium and cystatin C, an additional marker of kidney function
   3. Serum: bone markers and other markers of kidney disease progression including serum phosphate, alkaline phosphatase, intact parathyroid hormone (PTH) and fibroblast growth factor-23 (FGF-23) levels.

*Hypothesis: Treatment with vitamin D and calcium will result in better kidney function compared to placebo*.

*10.6.3 Recruitment and Enrollment Procedures*

The parent study defines the pool of potential subjects and those subjects who are willing to participate will be consented at the in-person End-of-Treatment visit (which is part of the parent study procedures) prior to their 3-year or 5-year follow-up colonoscopy. Participants will be reimbursed $15 for their time and effort after completion of the specimen collection.

*10.6.4 Specimen/data Collection and Analysis*

10.6.4.a Urine collection

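### Kidney ancillary study (Protocol 10.6.5): 900 participants give about 61% power for 3 mm Hg and 59% for a microalbuminuria relative risk of 0.64, not the stated >85% and 80%

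*Protocol*

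**What the plan says.** Section 10.6.5 sets the size of the sub-study: "we plan to recruit approximately 900 into this sub-study", out of 2259 in the parent trial. So 900 is a total across all arms.

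- **Microalbuminuria (primary aim).** "Assuming the background prevalence of microalbuminuria in the trial is 12% and an alpha of 0.05", the section states "80% power to detect a relative risk of 0.64 for microalbuminuria comparing the vitamin D groups to the placebo group with 900 participants". It then gives this as the reason for aiming at 900. The hypothesis in Section 10.6.2 is that "Vitamin D treatment will be associated with a lower prevalence of microalbuminuria", so 12% is the rate without vitamin D.
- **Blood pressure (secondary aim).** The section says that "the standard deviation for systolic blood pressure is approximately 20 mm Hg" and, with the same 900 participants, that "we will have greater than 85% power to detect a difference of 3 mm Hg between the vitamin D and placebo groups".

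Section 10.6.6 names the tests. Microalbuminuria is compared across randomized groups by chi-square. For blood pressure there is a four-group ANOVA and then a two-group test: "We will also compare vitamin D to no vitamin D using" Student's t-test.

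Section 10.6.5 does not say how the 900 divide between the compared groups, or whether alpha is one- or two-sided. In the parent trial, vitamin D is allocated 1:1 (Section 13.2 expects 1103 per group with follow-up) and significance is two-sided at 0.05 (Section 13.5).

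**The concern.** The inputs for a simple two-group power calculation are nearly all on the page, and a quick check misses both stated figures by more than 20 percentage points. The microalbuminuria figure matters more, because it concerns the sub-study's primary aim and is the stated ground for recruiting 900.

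At about 60% power, the chance of missing the stated effect is about 40%. The protocol implies 20% for microalbuminuria and less than 15% for blood pressure. Anyone relying on Section 10.6.5 would think the sub-study more informative about these effects than it is.

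**Working it through.** **Inputs from Section 10.6.5:** total 900; alpha 0.05; SD 20 mm Hg; difference 3 mm Hg; background prevalence 12%; relative risk 0.64, so 0.12 × 0.64 = 7.68% on vitamin D.

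**Assumptions from the parent trial:** 1:1 split, so 450 vs 450; two-sided test, so z = 1.96.

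**1. Blood pressure (stated: >85%).** Power = Φ(δ/SE − 1.96), with SE = SD·√(2/n).
- SE = 20·√(2/450) = 1.333
- 3/1.333 = 2.25
- Φ(2.25 − 1.96) = Φ(0.29) = **61.4%**

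**2. Microalbuminuria (stated: 80%).** Power = Φ((d − 1.96·SE₀)/SE₁), with the pooled SE₀ under the null and the unpooled SE₁ under the alternative.
- d = 0.12 − 0.0768 = 0.0432; mean rate = 0.0984
- SE₀ = √(0.0984 × 0.9016 × 2/450) = 0.01986
- SE₁ = √((0.12 × 0.88 + 0.0768 × 0.9232)/450) = 0.01980
- (0.0432 − 0.0389)/0.0198 = 0.216; Φ(0.216) = **58.6%**

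The plan's own figures therefore do not reproduce.

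**3. Variants on a total of 900.**

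| Variant | Blood pressure | Microalbuminuria |
|---|---|---|
| Stated in 10.6.5 | >85% | 80% |
| 450 vs 450, two-sided | 61.4% | 58.6% |
| 450 vs 450, one-sided | 72.7% | 70.3% |
| Unpooled, arcsine, log-RR or log-OR test | – | 57.6–59.0% |
| With continuity correction | – | 54.1% |
| Background 8.5% (the other survey figure cited) | – | 43.7% |
| 167 placebo-only vs 450 vitamin D, two-sided | 38% | 40% |

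An equal split is close to the most favourable division of 900, so another allocation does not help.

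**4. Placebo-only row.** The schema in Section 3.2 puts 360 + 84 = 444 of about 2400 in the placebo-only arm. Scaled to the sub-study, 900 × 444/2400 = 166.5, or about 167. This assumes that the sub-study mirrors the planned parent allocation.
- Blood pressure: SE = 20·√(1/167 + 1/450) = 1.812; Φ(3/1.812 − 1.96) = Φ(−0.30) = 38%.
- Microalbuminuria, with 12% in the 167 and 7.68% in the 450: mean rate (20.04 + 34.56)/617 = 0.0885; SE₀ = 0.0257; SE₁ = 0.0281; Φ((0.0432 − 0.0504)/0.0281) = Φ(−0.26) = 40%.

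**5. What 450 vs 450 can detect, two-sided.**
- Blood pressure, 80% power: (1.960 + 0.842) × 1.333 = 3.7 mm Hg.
- Blood pressure, 85% power: (1.960 + 1.036) × 1.333 = 4.0 mm Hg.
- Microalbuminuria, 80% power: solving step 2 for the relative risk gives about 0.55.

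**6. What the stated powers would need.**
- 85% for 3 mm Hg: 2 × 20² × (1.960 + 1.036)²/3², which rounds up to 799 per group, about 1,598 in total.
- 80% for a relative risk of 0.64: (1.96·√(2 × 0.0984 × 0.9016) + 0.842·√(0.1056 + 0.0709))²/0.0432², which rounds up to 746 per group, about 1,492 in total.

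**The case against.** The strongest reply is that the split and the sidedness are not in Section 10.6.5, so 61% and 59% rest on inputs borrowed from the parent trial. That is correct and has to be labelled. It does not save the stated figures: a one-sided test still falls short of both, and other splits offer essentially nothing better.

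A second reply concerns the SD. Section 10.6.6 analyses the mean of three readings, and the 20 mm Hg comes from an outside cohort. An SD of 15 would give 85.1%. But the protocol's planning value is 20, and nothing in it supports 15. Nor is a gain from baseline adjustment planned: Section 10.6 collects urine and blood pressure at the end-of-treatment visit, and covariate adjustment is foreseen only if the groups are imbalanced.

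A third reply is about weight. This is an optional ancillary study that Section 10.6.6 itself calls post hoc. That stands, and it limits the severity.

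A reader might also infer more than the documents support:

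- **How the errors arose.** Treating 900 as a per-group number gives 88.9% for blood pressure. Placing 12% in the vitamin D group against 18.75% in controls gives 80.25% for microalbuminuria. These are numerical coincidences as far as the text shows. The protocol gives no derivation, so neither origin should be asserted.
- **How a null result would be read.** Section 10.6 contains no interpretation rule, so a claim that a null result will be misread is a prediction.
- **That the comparison is settled.** Vitamin D vs no vitamin D is explicit only for the blood pressure t-test. Section 10.6.2 frames the aims as each active regimen against placebo, so the choice belongs to the authors.

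**Conclusion.** Both power statements in Section 10.6.5 are wrong on the section's own inputs. With 450 vs 450 and two-sided alpha 0.05, power is about 61% rather than more than 85% for 3 mm Hg, and about 59% rather than 80% for a relative risk of 0.64. If the placebo-only arm is meant, with about 167 participants assumed, the figures are about 38% and 40%.

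The conclusion rests on 900 being the total, which the text makes plain, and on the SD of 20 and prevalence of 12% as stated. The exact values also depend on the parent trial's allocation and sidedness; the conclusion that both powers are overstated does not.

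This should be fixed, and it is confined to the ancillary study. It does not show that the trial as a whole is underpowered, because the sample size in Section 13.2 does not depend on it.

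**What to change.** Restate Section 10.6.5 and leave enrolment at about 900:

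- **Microalbuminuria:** with 450 vs 450 and two-sided alpha 0.05, 80% power for a relative risk of about 0.55, and about 59% at 0.64.
- **Blood pressure:** on the same basis with SD 20 mm Hg, 85% power for about 4.0 mm Hg, and about 61% at 3 mm Hg.
- **Assumptions:** state the expected split, the sidedness and the comparison. The figures above hold for vitamin D vs no vitamin D. If the placebo-only arm is the intended comparator, recompute them with its expected size.

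The sentence that derives the target of 900 from 80% power at 0.64 should be reworded to match. The cost is a text change; no participants, procedures or analyses are added.

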4. Subjects will be sent materials describing this new development. All subjects who were randomized into the study will be sent these materials with the sole exception of deceased subjects. The materials include:

a. Letter to Subject with Normal Creatinine Result

b. Letter to Subject with Above Normal Creatinine Result

c. Above normal creatinine result with specific result and lab range

d. Significant New Information/Findings sheet for Pre-EOT subjects

e. Significant New Information/Findings sheet for Post-EOT subjects

f. Post-EOT Additional Study Visit Consent

1. Subjects who choose to discontinue study calcium treatment will be urged to continue study vitamin D treatment.

6.3.2 April 11, 2012 modification to the creatinine criteria and procedures to be used due to the Unanticipated Problem

1. Because many of the local laboratories used for creatinine measurements in the study do not take sex, age or race into account, the creatinine reference ranges provided by those laboratories may not be appropriate for the individual subject. Therefore, the criteria for stopping study calcium treatment (randomized or two-arm) has been changed to an increase of 0.3 mg/dL or more from baseline (update to #1 in section 6.3.1 above, originally implemented in October 2011).
2. Similarly, subjects who complete or who already have completed the treatment phase of the study and whose last creatinine level in the study was increased by 0.3 mg/dL or more from baseline will be invited to return for a blood draw to re-measure the levels (update to #3 in section 6.3.1 above, originally implemented in October 2011).
3. In place of annual study blood draws during the treatment phase or a study visit after completion of the treatment phase, creatinine (and calcium) levels may be documented from medical records.

*6.4 Colonoscopy*

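### The serial creatinine analysis drops a whole participant for one off-laboratory value, contradicting its stated all-participant population; the laboratory rule should apply to values, not persons

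*Protocol*

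**What the plan says.** Section 10.6.5 (Sample Size and Power) says of the repeated-measures creatinine analysis: "we will only use data from participants who have had all of their creatinines measured at the same laboratory". It puts the resulting number at about 1500. The parent-study total is in the same section: "Of the 2259 participants in the parent study, we plan to recruit approximately 900 into this sub-study".

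Section 10.6.2 sets the same aim, at baseline and years 1, 3 and 5, "in all participants of the parent study with available creatinine measurements". The introduction to 10.6 agrees. It commits the baseline, year-1 and year-3 values, and the end-of-treatment (EOT) values, of all randomized subjects to these analyses.

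The laboratory for the EOT value is described in more than one way. Section 10.6.2 has "creatinine (to be assayed at the lab used for baseline measurement", and 10.6.4.d sends creatinine to local laboratories. Section 10.6.4.e lists serum creatinine among the assays of the central research laboratory.

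Section 6.3.2, added after the 2011 unanticipated-problem report, brings in further values. People who have completed treatment and "whose last creatinine level in the study was increased by 0.3 mg/dL or more from baseline will be invited to return" for re-measurement. In place of that visit, or of the annual on-treatment draws, "creatinine (and calcium) levels may be documented from medical records".

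For serial creatinine, section 10.6.6 plans random-effects models and notes that they can handle missing values.

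**The concern.** The protocol defines two populations for one analysis and does not reconcile them. The narrower one is a person-level rule. If any one of a participant's creatinines comes from another laboratory, all of that participant's values go, including a baseline and year-1 pair measured in the same place. Whether this happens is decided after randomization, so the retained group is no longer the randomized group.

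The trial added renal procedures after a safety report, so serial creatinine by treatment arm is a comparison that readers will look at closely. Three things are at stake: randomized data lost without need, a comparison no longer fully protected by randomization, and an analysis set that cannot be reproduced because the protocol does not say which creatinines count.

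**Working it through.** **1. Number outside the rule.** Inputs, both from 10.6.5: 2259 participants and about 1500 retained. 1500/2259 = 66.4% kept. 2259 − 1500 = 759, and 759/2259 = 33.6% outside.

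**2. The plan's own power figure.** Section 10.6.5 reads "Having a sample size of 1500 for repeated measures analysis to evaluate changes in creatinine with an alpha of 0.05" and claims 90% power for 0.1 mg/dL. No SD, within-person correlation or group split is given, so the figure can be neither reproduced nor refuted. Solving backwards with a two-sided test of means:

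SD = 0.1 / [(1.960 + 1.282) × √(1/n₁ + 1/n₂)]

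- 750 v 750: SD ≈ 0.60 mg/dL
- 375 v 375: SD ≈ 0.42 mg/dL

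With SD 0.60 and two equal groups, power is 0.90 at 1500 in total and 0.98 at 2259. A value-level rule would fall between these, so the case for it is the analysis population more than power.

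**3. Which later values could trigger exclusion.**

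| Source of value | Who has it | Selected on a rise? | Laboratory stated? |
|---|---|---|---|
| Annual on-treatment draws (6.3.1) | everyone still on treatment | no | not in 6.3.1; section 9.1 says local |
| Medical-record substitutes for those draws (6.3.2) | anyone on treatment | no | no |
| Stored EOT specimens (6.3.1) | those who had already completed treatment | no | no |
| Post-treatment re-measurement, or its medical-record substitute (6.3.2) | those whose last value rose by at least 0.3 mg/dL | yes | no |

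Only the last row depends on the outcome. The protocol does not say whether that value is among the creatinines that must share a laboratory.

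**4. Consistency of the stated n.** If central-laboratory creatinine counted for all of the roughly 900 sub-study participants, at most 2259 − 900 = 1359 people could satisfy the rule. That is below the stated 1500, so 10.6.4.e and 10.6.5 cannot both be read at face value.

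**5. Whether a direction of bias can be derived (illustration; all rates assumed except 33.6%).** Let x be the true proportion with a rise, d₁ the share of those with a rise who are excluded, and d₀ = 0.336 the share of the others excluded.

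Retained proportion = x(1 − d₁) / [x(1 − d₁) + (1 − x)(1 − d₀)]

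Take true proportions of 3% (control) and 6% (treated), a ratio of 2.0 and a difference of 3.0 points.

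- d₁ = 0.336 in both arms: 3.0% v 6.0%, ratio 2.0.
- d₁ = 0.50 in both arms: 0.015/0.659 = 2.28% v 0.030/0.654 = 4.59%. The ratio stays about 2.0 and the difference falls to 2.3 points.
- d₁ = 0.336 control, 0.60 treated: 3.0% v 0.024/0.648 = 3.70%, ratio 1.23.
- d₁ = 0.60 control, 0.336 treated: 0.012/0.656 = 1.83% v 6.0%, ratio 3.28.

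Equal loss leaves the ratio nearly unchanged. Unequal loss can move it either way. The planned model compares creatinine levels rather than proportions with a rise, so these figures show only that the direction is undetermined.

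**The case against.** A reader might infer that the rule removes mainly participants whose creatinine rose, and so hides a renal harm. The document does not support this. The rule is stated only for the repeated-measures analysis. The CKD comparison across the four arms, cystatin C and albuminuria carry no such limit. Most of the added measurements apply whether or not creatinine rose, and nothing sends re-draws to a different laboratory. Sections 10.6 and 10.6.2 name only baseline, years 1, 3 and 5 and the EOT visits, so the one rise-selected re-measurement may not count at all. These points stand.

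It is also fair to say that a same-laboratory restriction is a sensible guard against between-laboratory differences when the target is 0.1 mg/dL. Some of the 759 may simply lack follow-up values. And a value-level rule would still set an off-laboratory high value to missing. All of that is accepted.

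None of it reconciles 10.6.5 with 10.6 and 10.6.2, or justifies discarding a person's same-laboratory values when the planned model does not need complete records. Nor is this a detail left to an analysis plan, because the protocol itself fixes the exclusion.

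**Conclusion.** The point holds for the repeated-measures creatinine analysis only. The protocol gives that analysis two incompatible populations. The narrower one leaves out about 759 of 2259 participants (34%), conditions on a post-randomization feature, and discards valid within-laboratory pairs. Its text on the EOT laboratory conflicts, and one reading caps the eligible number at 1359, below the stated 1500.

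Outcome-related exclusion is possible, because one route to an outside value opens only after a rise of at least 0.3 mg/dL. It requires that such values count towards the rule and come from another laboratory, and the protocol states neither. No size or direction of bias should be claimed.

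The 34% takes the stated n≈1500 at face value and does not separate off-laboratory exclusions from participants with no follow-up creatinine.

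**What to change.** Make these changes to the analysis wording:

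- **Population.** Include every randomized participant with a baseline creatinine and at least one later scheduled value (year 1, year 3, or year 5/EOT) from the same laboratory. Use this definition in 10.6, 10.6.2 and 10.6.5.
- **Off-laboratory values.** Set them to missing in the random-effects model of 10.6.6, and state the missing-at-random assumption this relies on.
- **Sensitivity analysis.** Fit the model to all available values with a term for laboratory.
- **Triggered re-measurements.** State that post-treatment values obtained because of a rise do not determine who is included.
- **EOT laboratory.** Reconcile 10.6.2 and 10.6.4.d with 10.6.4.e on which EOT creatinine enters the serial analysis, then restate the n and give the SD behind the power claim.

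The cost is small. The laboratory must be known for each value, which the present rule already requires. The remaining limitation is that off-laboratory values inform only the sensitivity analysis.
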